## **Mediterranean diet effects on vascular health and serum levels of adipokines and ceramides.**

### **A Randomized Trial. *Trial protocol***

#### **Background**

Current knowledge of complex interplays between nutrients and other food constituents has driven to a better knowledge of the concept of total dietary patterns. The concept of a "dietary scheme" has been progressively used to involve a complete and exhaustive analysis of food and nutrient consumption in particular dietary pattern.

Current knowledge highlights the crucial role of the Mediterranean-style diet in the prevention of cardiovascular diseases. The Lyon diet heart study reported the beneficial effects of the Mediterranean-style diet on the secondary prevention of cardiovascular diseases (4).

The PREDIMED (Prevention with Mediterranean Diet) study is the first large-scale randomised trial that reported the effectiveness of the Mediterranean-style diet in primary prevention in terms of reduction of incidence cardiovascular events, such as strokes, atrial fibrillation, peripheral vascular disease, and myocardial infarction .

This study showed that adherence to the Mediterranean-style diet supplemented with extra virgin olive oil or walnuts obtained a significant reduction of cardiovascular events in comparison to the control group randomized to a low-fat diet.

Cardiovascular disease, which includes coronary artery disease, cerebrovascular disease, peripheral artery disease and heart failure, is the leading cause of mortality worldwide. Atherosclerosis is the main cause of cardiovascular diseases, particularly coronary artery disease and stroke; it is a disease with a possible genetic , metabolic, environmental and behavioural based-pathogenesis.

Hypercholesterolemia is the main metabolic risk factor of atherosclerosis . Several studies have reported that reducing fat in diet reduces the levels plasma cholesterol and it is associated to a lower incidence of coronary heart disease; this effect has been reported in particular with saturated fat reduction and with its replacing with polyunsaturated and monounsaturated fat of virgin olive oil.

However, the need for additional predictive biomarkers is underlined by the very substantial residual risk that exists above the standard clinical and biochemical risk predictors. Ceramides are members of the sphingolipid family and precursors of complex sphingolipids. Some studies in cultured cells and animal models reported that the accumulation of ceramides may lead to the activation of pathologic pathways altering normal cellular function, including the action of insulin. Thus the excess de novo ceramide biosynthesis may be due to cellular stress stimuli, such as high serum levels of saturated free fatty acids. Ceramide and its metabolites represent an intermediate link between over-nutrition and the pathogenetic basis of the cardiometabolic disease risk, including insulin resistance and low-grade inflammation. Thus it appears worthy of interest the evaluation of the role of serum ceramide levels as an expression of the interplay between lipidemic pathways and vascular health status.

Adipocytes produce some hormones that directly interplay with the local microenvironment as well as distant tissues. Thus adipocytes have a possible pathogenetic role in the development of cardiometabolic diseases. Some adipokines produced by adipose tissue have been reported to be linked to inflammation and atherosclerosis and its related cardiovascular complications.

Few studies have prospectively analyzed the association between ceramides and the incidence of cardiovascular and cerebrovascular events. Laaksonen et al. reported a not well clear relationship of plasma ceramides with death from cardiovascular disease (CVD). It has been also suggested a possible role of the ratio of two ceramides as a possible predictive factor cardiovascular risk. The PREDIMED study suggested that dietary interventions according to a Mediterranean-style diet positively modified the association between a blood ceramide score (comprised of individual ceramides and ceramide ratios) and risk of incident CVD.

Furthermore, The CORDIOPREV in patients with established coronary heart disease randomly to receive a Mediterranean diet or a low-fat diet intervention, with a follow-up of 7 years analyzed the primary outcome of a composite of major cardiovascular events, including myocardial infarction, revascularisation, ischaemic stroke, peripheral artery disease, and cardiovascular death. Authors

concluded that in secondary prevention, the Mediterranean diet was superior to the low-fat diet in preventing major cardiovascular events.

Nevertheless no study have evaluated in the same study the effects of Mediterranean Diet on endothelial function in parallel to its effects on serum lipid change including serum ceramide changes and on some adipokine serum pathway.

On this basis we designed a randomized trial to evaluate the effects of Mediterranean diet on endothelial function measured by the evaluation of reactive hyperaemia index (RHI) and the diet effects on serum ceramide and adipokines levels.

## **Methods**

### **Patients and recruitment**

consecutive patients at high risk of cardiovascular diseases admitted to the Internal Medicine and Stroke Care ward at the University Hospital of Palermo between September 2017 and December 2020 will be enrolled

The enrolled patients will be male subjects aged between 55 and 80 and female subjects between the ages of 60 and 80 who tested positive for at least two of the following eligibility criteria thus to be classified as subjects at high cardiovascular risk

- 1) Type 2 diabetes mellitus
- 2) Arterial hypertension
- 3) Body mass index (BMI)  $\geq 25$
- 4) Active smoking
- 5) Family history of early cardiovascular disease
- 6) Previous cardiovascular or cerebrovascular events (> 6 months)

### **Exclusion criteria**

All patients with recent (<6 months) cardiovascular or cerebrovascular events were excluded

## **Randomization**

The enrolled subjects, after the evaluation of the degree of adherence to a dietary regimen of the Mediterranean-style diet, were randomised

to two different types of dietary schemes:

1. Group A (experimental arm) - Mediterranean Diet : adherence to a Mediterranean-style diet was assessed through dietary screening at each follow up visit (every three months) for the entire duration of the study (twelve months).
2. Group B (control arm) - Low-fat diet: for which the enrolled subjects received dietary "counselling" starting from their first visit at the time of enrolment and, subsequently, every three months for the entire duration of the study (twelve months).

The randomization code was based on computer-generated random numbers and a 2:1 randomization ratio for experimental/control arm was performed both to contain the high cost of clinical investigations to be performed, and to avoid the effects of a high drop out rate by allowing more power for a per-protocol analysis. As a consequence of the type of randomization chosen, in order to maintain the power of the study, an increase in sample size of 12% was planned.

The investigators involved in clinical data collection and the measurement of outcome variables were not directly involved in the patients' treatment and were masked to the randomization process. The randomization code was maintained only at the central data facility and was not broken until all data analysis was complete

## **Dietary Intervention Trial**

We will adopt the dietary intervention protocol with regard of Mediterranean Diet and low-fat diet validated by the PREDIMED trial (5).

**A. Mediterranean Diet** : The general guidelines to follow the Mediterranean diet that researchers will provide to participants included the following positive recommendations: a) abundant use of olive oil for cooking and dressing dishes; b) consumption of  $\geq 2$  daily servings of vegetables (at least one of them as fresh vegetables in a salad), discounting side dishes; c)  $\geq 2$ -3 daily servings of fresh fruits (including natural juices); d)  $\geq 3$  weekly servings of legumes; e)  $\geq 3$  weekly servings of fish or seafood (at least one serving of fatty fish); f)  $\geq 1$  weekly serving of nuts or seeds; g) select white meats (poultry without skin or rabbit) instead of red meats or processed meats (burgers, sausages); h) cook regularly (at least twice a week) with tomato, garlic and onion adding or not other aromatic herbs, and dress vegetables, pasta, rice and other dishes with tomato, garlic and onion adding or not aromatic herbs. This sauce is made by slowly simmering the minced ingredients with abundant olive oil. Negative recommendations are also given to eliminate or limit the consumption of cream, butter, margarine, cold meat, pate, duck, carbonated and/or sugared beverages, pastries, industrial bakery products (such as cakes, donuts, or cookies), industrial desserts (puddings, custard), French fries or potato chips, and out-of-home pre-cooked cakes and sweets. The researchers insisted that two main meals per day should be eaten (seated at a table, lasting more than 20 minutes). For usual drinkers, the advice was to use wine as the main source of alcohol (maximum 300 ml, 1-3 glasses of wine per day). If wine intake was customary, a recommendation to drink a glass of wine per day (bigger for men, 150 ml, than for women, 100 ml) during meals was given. Ad libitum consumption was allowed for the following food items: nuts (raw and unsalted), eggs, fish (recommended for daily intake), seafood, low-fat cheese, chocolate (only dark chocolate, with more than 50% cocoa), and whole-grain cereals.

**B. Control diet group.** A low-fat, high complex carbohydrate diet, as recommended by the National Cholesterol Education Program, with  $<30\%$  of total calories from fat (12 -14% MUFAs, 6-8% PUFAs,  $< 10\%$  SFAs), 55% from carbohydrates and 15% from protein. In both diets, the cholesterol content was adjusted to  $<300$  mg/day (6). The focus in the control group was to reduce all types of fat, with

particular emphasis in recommending the consumption of lean meats, low-fat dairy products, cereals, potatoes, pasta, rice, fruits and vegetables.

### **Data collection/analysis**

#### **Evaluation of adherence to the Mediterranean and to the low-fat diet**

For participants in the Mediterranean-diet group, researcher will undertake individual and group dietary-training sessions at the baseline visit and every three months thereafter. In each session, participants completed a 14-item dietary questionnaire to assess adherence to the Mediterranean diet so that personalized advice could be provided to the study participants in these groups.

Information relating to the dietary habits of the enrolled patients will be collected through a specific questionnaire (semiquantitative food frequency questionnaire (F.F.Q.s) (17) dedicated to the evaluation of the frequency of different food items in the diet and adapted to the Sicilian population. The subjects enrolled were classified based on the levels of adherence to a Mediterranean-style diet according to the methods proposed by Trichopoulou et al. (18).

The patients enrolled in the study will be assessed for their adherence to a dietary regimen of the Mediterranean-style diet using the Mediterranean Diet Score, and the quantity and frequency of consumption of the food items characterising a Mediterranean-style diet were evaluated.

The consumption of foods presumed to be far from this diet pattern (i.e., rare or monthly consumption, meat and meat products, poultry and complete fat products) will be assigned scores on an inverse scale. A value of 0 or 1 will be assigned to each indicated food component. For the beneficial components, patients whose consumption was below the median were assigned a value of 0. For components presumed to be detrimental, patients whose consumption was below the median were assigned a value of 1.

We will apply a non-monotonous function for the alcohol, i.e., score 5 for the consumption of less than 300 ml of alcohol per day, score 0 for no consumption or for the consumption of > 700 ml per

day and scores from 4 to 1 for the consumption of 600-700, 500-600, 400-500 and 300-400 ml per day (100 ml is equivalent of 12 g ethanol).

Participants in the control group also will receive a dietary training at the baseline visit and completed the 10-item questionnaire at baseline to assess their adherence to the Mediterranean diet. During admission visit of the study, they received a leaflet explaining the low-fat diet on three month basis and assessing adherence to this low-fat diet with the use of a separate 9-item dietary questionnaire. Scores ranged from 0 to 9, with higher scores indicating greater adherence to a low-fat diet.

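### The alcohol item of the Mediterranean Diet Score is inverted between 300 and 700 ml/day and runs from 0 to 5 beside food components scored 0 or 1

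*Protocol*

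**What the plan says.** Under Evaluation of adherence to the Mediterranean and to the low-fat diet, the protocol builds a Mediterranean Diet Score from food-frequency data and uses it to grade participants: "The subjects enrolled were classified based on the levels of adherence to a Mediterranean-style diet".

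- **Food components.** "A value of 0 or 1 will be assigned to each indicated food component", split at the median, with the direction reversed for foods presumed detrimental.
- **Alcohol, general rule.** "We will apply a non-monotonous function for the alcohol".
- **Alcohol, ends of the scale.** "score 5 for the consumption of less than 300 ml of alcohol per day" and "score 0 for no consumption or for the consumption of > 700 ml per" day.
- **Alcohol, middle bands.** "scores from 4 to 1 for the consumption of 600-700, 500-600, 400-500 and 300-400 ml per day".
- **Conversion.** "100 ml is equivalent of 12 g ethanol".

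The section does not state how many food components there are, what cut-offs define the adherence levels, or whether the alcohol item is rescaled before it is added to the rest.

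**The concern.** Two features of the alcohol item look wrong.

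The first is the order of the middle bands. Both scores and bands are given as lists. Paired item by item, the heaviest of the four bands gets the most points and the lightest gets the fewest. A score meant to peak at low intake and reach zero at very high intake should fall between those ends, but this one rises.

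The second is the scale. One item can contribute five points and every other item at most one, with nothing to bring them to a common range.

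The score matters because it is a stated measure of adherence. The Aims section words all three aims as effects of adherence to the diet, and the Randomization section gives power for a per-protocol analysis as one reason for the 2:1 ratio. An adherence-based analysis that drew on this score would inherit both faults.

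**Working it through.** **Inputs, all from the section quoted above:** the alcohol points and bands, 12 g ethanol per 100 ml, and 0 or 1 per food component. The number of food components is not given; 6 to 10 is assumed below to show a range.

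**Step 1: points by intake.** Grams = ml × 12/100, at the band midpoint. The last column shows the points if the four middle scores are put in falling order.

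| Intake (ml/day) | Ethanol at midpoint | Points as listed | Points in falling order |
|---|---|---|---|
| none | 0 g | 0 | 0 |
| under 300 | 150 × 0.12 = 18 g | 5 | 5 |
| 300-400 | 350 × 0.12 = 42 g | 1 | 4 |
| 400-500 | 450 × 0.12 = 54 g | 2 | 3 |
| 500-600 | 550 × 0.12 = 66 g | 3 | 2 |
| 600-700 | 650 × 0.12 = 78 g | 4 | 1 |
| over 700 | over 84 g | 0 | 0 |

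As listed, the score loses 4 points at 300 ml, regains 3 by the 600-700 ml band, then loses 4 above 700 ml. The 78 g/day drinker outscores the 42 g/day drinker by 4 − 1 = 3 points, the value of three food components. In falling order the same pair differ by 3 points the other way.

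**Step 2: does the declared shape explain it?** A non-monotonic function accounts for 0 at no intake, a peak at low intake and 0 at very high intake. The falling-order column already has that shape. It does not account for a second climb between 300 and 700 ml. The two ends of the protocol's own scale point to a reversed list in the middle.

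**Step 3: weight of the item.** Alcohol maximum ÷ food-component maximum = 5/1 = 5. With k food components, alcohol's share of the maximum score is 5/(k + 5):

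- k = 6: 5/11 = 45%
- k = 8: 5/13 = 38%
- k = 10: 5/15 = 33%

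Scored 0 or 1 like the foods, the share would be 1/(k + 1): 1/7 = 14% at k = 6 and 1/11 = 9% at k = 10.

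This does not depend on how the middle bands are read. An abstainer and a drinker below 300 ml differ by 5 − 0 = 5 points, or five food components. With k = 8, an abstainer who meets every food item (8 + 0 = 8) ties with a drinker below 300 ml who meets three (3 + 5 = 8).

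**The case against.** The strongest reply concerns reach, and most of it stands.

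- **The inversion is local.** It touches only the four bands from 300 to 700 ml/day. The ends run the expected way, and the order may be a drafting slip. A reader might infer that heavy drinkers are ranked above moderate ones in general. The text does not support that: drinkers below 300 ml, the wine maximum in the Mediterranean arm's dietary advice, score highest, and those above 700 ml score 0. Someone who codes the text as written will still get the middle bands wrong.
- **The score is not an endpoint.** RHI, lipids, ceramides and adipokines are not calculated from it. The protocol mentions a per-protocol analysis but does not define that set by this score, and it specifies no adherence-response analysis. It also has a 14-item questionnaire for the Mediterranean arm and a 9-item one for the low-fat arm. It would therefore be too strong to conclude that every adherence analysis is wrong.
- **Repeat scoring is not stated.** The text does not say that this score is taken at every visit. If it only describes participants at baseline, errors in it do not bias the randomised comparison.
- **Unequal weights are not in themselves a contradiction.** Alcohol has its own explicit rule, and the cited scoring method cannot be consulted here. It may also be tempting to say that alcohol dominates the score. A share of the maximum is not a share of variance or of classifications, so that is not shown.

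What remains is a scoring rule that contradicts its own end points, and a fivefold weight that the protocol neither rescales nor explains.

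**Conclusion.** The point holds as an error in a stated scoring rule. Across 300 to 700 ml/day the alcohol points run in the opposite direction to the scale's own ends, with errors of 3, 1, 1 and 3 points over the four bands relative to falling order. Separately, the item carries five times the weight of any food component. That is about 33% to 45% of the maximum score, on the assumption of 6 to 10 food components.

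Any adherence classification or analysis that uses this score would be distorted. The number of patients affected cannot be computed, because the component count, the class cut-offs and the distribution of intake are not given. The documents do not show bias in the randomised comparison of RHI, lipids, ceramides or adipokines.

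**What to change.** 1. Replace the sentence with a scoring table in which points fall from 4 to 1 across 300-400, 400-500, 500-600 and 600-700 ml/day. Assign 400, 500 and 600 ml to one band each, since each limit now belongs to two.
2. Reconcile the alcohol item with the 0/1 food components on one common scale, and state the number of components and the maximum score.
3. Recompute the score with that table wherever it was taken, before it enters any analysis.

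The cost is one corrected table and a re-run of the score from questionnaire data that the protocol already collects. No new data are needed. The change concerns scoring only and leaves the drinking advice untouched.

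### The alcohol item of the Mediterranean Diet Score lists its middle bands in the wrong order, so between 300 and 700 ml a day heavier drinking scores as better adherence (minor, wrong as written)

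*Protocol*

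**What the plan says.** The rule stands in the protocol section Evaluation of adherence to the Mediterranean and to the low-fat diet. For foods, "A value of 0 or 1 will be assigned to each indicated food component". Alcohol is treated separately: "We will apply a non-monotonous function for the alcohol". One sentence then fixes the whole item:

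- Moderate intake: "score 5 for the consumption of less than 300 ml of alcohol per day".
- Both extremes: "score 0 for no consumption or for the consumption of > 700 ml" a day.
- The range between: "scores from 4 to 1 for the consumption of 600-700, 500-600, 400-500 and 300-400 ml per day".
- Conversion: "100 ml is equivalent of 12 g ethanol".

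The same section says what the diet score is for: "The subjects enrolled were classified based on the levels of adherence to a Mediterranean-style diet".

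The section Dietary Intervention Trial separately advises usual drinkers in the Mediterranean arm on wine: "maximum 300 ml, 1-3 glasses of wine per day". No other part of the protocol gives an order for the alcohol bands.

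**The concern.** The two ends of the sentence show which way the item is meant to run. Drinking something, but under 300 ml, is best; drinking over 700 ml is as bad as the scale allows. Points in between should therefore fall as intake rises. The middle clause pairs a descending list of scores with a descending list of intakes, so the points rise with intake instead.

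The declared non-monotonic shape does not account for this. Giving 0 to abstainers, 5 to moderate drinkers and 0 to heavy drinkers already makes the function non-monotonic, whichever way the middle bands run. The printed order adds a second peak at 600-700 ml, which nothing in the text calls for.

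At stake is the ranking of adherence among participants who drink between 300 and 700 ml a day. Anyone who codes the item literally gives these participants scores in reverse order, and the diet score is the measure by which the protocol classifies adherence.

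**Working it through.** **Inputs**, all from the alcohol sentence: 5 points below 300 ml; 0 points for none or above 700 ml; scores 4, 3, 2, 1 set in order against 600-700, 500-600, 400-500 and 300-400 ml; 12 g ethanol per 100 ml, that is 0.12 g per ml.

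**Step 1. Printed score.** Match each score to the band in the same position, then sort by rising intake. The intended score keeps both end points and lets the points fall by one per band, which for the four middle bands is 5 minus the printed score.

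| Intake per day | Ethanol (ml x 0.12) | Printed | Intended | Printed minus intended |
|---|---|---|---|---|
| none | 0 g | 0 | 0 | 0 |
| above 0, below 300 ml | below 36 g | 5 | 5 | 0 |
| 300-400 ml | 36-48 g | 1 | 4 | -3 |
| 400-500 ml | 48-60 g | 2 | 3 | -1 |
| 500-600 ml | 60-72 g | 3 | 2 | +1 |
| 600-700 ml | 72-84 g | 4 | 1 | +3 |
| above 700 ml | above 84 g | 0 | 0 | 0 |

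**Step 2. Shape.** By rising intake the printed item runs 0, 5, 1, 2, 3, 4, 0. It drops 5 - 1 = 4 points at 300 ml, climbs one point per band, then drops 4 - 0 = 4 points at 700 ml. The intended item runs 0, 5, 4, 3, 2, 1, 0: one peak, then steps of one point. Both sequences are non-monotonic.

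**Step 3. Ranking.** Four bands form 4 x 3 / 2 = 6 pairs, and all six are ordered the wrong way round. For example, 350 ml is 350 x 0.12 = 42 g and scores 1; 650 ml is 650 x 0.12 = 78 g and scores 4. So 78 - 42 = 36 g more ethanol a day gains 3 points where it should lose 3. Comparisons with the other categories keep their direction: every middle band still scores below 5 and above 0.

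**Step 4. Band edges.** 400, 500 and 600 ml each belong to two bands as printed. Exactly 300 ml is not below 300, so it falls in the 300-400 band and scores 1. If 300 ml is meant to be acceptable, as the wine advice suggests, it should score 5. Of that gap of 5 - 1 = 4 points, 3 come from the reversed order (4 - 1) and 1 from the edge (5 - 4).

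**The case against.** The strongest reply is that this is a transposition, not a chosen rule. The sentence does not say that scores and bands correspond one to one, so the pairing is an inference; the end points make the descending order easy to recover, and staff may well have scored it that way. Most of this stands. It is probably a slip, and nothing in the protocol shows that any participant was scored in the printed order, so rescoring must be conditional. But in-order pairing is the natural reading, no other text corrects it, and a scoring rule should not depend on the coder noticing the mistake.

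A second reply is that little hangs on the item. That also stands. The Mediterranean group additionally completes a 14-item questionnaire and the controls a 9-item one. The protocol does not use the Mediterranean Diet Score for eligibility, stratification, exclusion or an endpoint.

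Three stronger readings are tempting, and the protocol supports none of them.

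- Because the aims are worded in terms of adherence, a reader might infer that the trial's results are biased. No analysis is tied to this score, and the comparison is between randomised diets.
- Because foods score 0 or 1, a reader might equate a 3-point error with three food components. The protocol does not say how the alcohol points enter the total, so that equivalence cannot be established.
- A reader might infer that the wine advice is itself wrong or contradicts the score. It is advice on wine to usual drinkers in one arm, whereas the score grades alcohol intake. Its 300 ml maximum bears only on which band exactly 300 ml should join.

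**Conclusion.** The point holds as a minor error in the text. As printed, the alcohol item reverses the order of the four bands between 300 and 700 ml a day and contradicts its own end points. The misstatement is 3 points in the two outer bands and 1 point in the two inner bands, with the lighter drinkers scored too low and the heavier ones too high. Abstainers, drinkers below 300 ml and drinkers above 700 ml are scored as intended.

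The conclusion rests on two readings: that scores and bands are paired in listed order, and that the 5 and 0 at the ends show the intended direction. The protocol does not say how many participants drink 300-700 ml a day, nor where the cut-offs for adherence lie, so the number misclassified, if any, cannot be estimated. No effect on endpoints, sample size or analysis sets is claimed.

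**What to change.** Rewrite the one sentence so that each intake has one score:

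- none, or above 700 ml: 0
- above 0 and up to and including 300 ml: 5
- above 300 to 400 ml: 4
- above 400 to 500 ml: 3
- above 500 to 600 ml: 2
- above 600 to 700 ml: 1

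This reverses the order, assigns each shared edge to one band, and brings exactly 300 ml into line with the maximum in the dietary advice. The section Dietary Intervention Trial needs no change.

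Then check how the item was actually coded. If the descending order was used, correct the text and settle any intakes lying exactly on an edge. If the printed order was used, rescore from the recorded intake. Where only the points were kept, replacing each score of 1 to 4 by 5 minus that score repairs everyone except participants exactly on an edge (300, 400, 500 or 600 ml). The cost is one sentence and, at most, recoding one item; no new data, visits or patients are needed.
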